# 4. METHODS OF INVESTIGATION

The clinical examinations including vital signs as well as safety assessments will be performed as usual in routine clinical practice.

The procedure for arthroscopy and biopsy handling to obtain tissue samples for the immunohistochemical assessments will be outlined in Appendices, which will be affixed to this protocol. The studies of synovial tissue will be performed at the Laboratory for Experimental Immunology/Division of Clinical Immunology and Rheumatology, Academic Medical Center, Amsterdam, The Netherlands. The studies of lesional skin will be performed at the Experimental Laboratory for Dermatology, Academic Medical Center, Amsterdam, The Netherlands.

Routine laboratory (hematology, chemistry and urinalysis as mentioned before) will be performed at all 4 study visits. Furthermore, blood will be drawn at the 2 arthroscopy visits at baseline and week 4 (3 heparin tubes, 1 serum tube, 1 EDTA tube at each time point). Mononuclear cells (PBMCs) will be isolated and stored in liquid nitrogen. Serum and plasma will be immediately frozen at -70°C. The material will be used for detection of biologic markers (such as cytokines), leukocyte differential, and gene activation (micro-array) in relation to the disease. All samples must be clearly labeled (using labeling that can withstand freezing in liquid nitrogen/dry ice) including patient number (and patient’s date of birth) and date and time of sampling.

## **Efficacy criteria**

#### *Analysis of the cell infiltrate and expression of mediators of inflammation of synovial tissue (and lesional skin)*

The effects of adalimumab compared to placebo on immunohistochemical indices for synovial inflammation and psoriatic skin lesions will be assessed on biopsies obtained by arthroscopy and by skin biopsies (4mm punch biopsy) from a target lesion.

## **Statistical methods**

The evaluation will comprise a description of the study population, a comparison of baseline values and the changes in the synovial features and clinical parameters after treatment with adalimumab for 4 weeks. The clinical evaluation after 12 weeks of treatment will be used to compare clinical response at 12 weeks to the synovial tissue response at 4 weeks. In addition, we will describe the clinical effects at each time point in all patients.

The findings will be tested for normal distribution. If this requirement is not fulfilled, appropriate non-parametric methods will be used. All statistical tests will be two-tailed and performed at the 5% significance level.

In addition, each of the end points will be statistically analyzed using an analysis of covariance (ANCOVA) model. The model included terms for treatment as a fixed effect and the baseline measurement as a covariate. The aim is to assess the treatment difference.

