## **Design**

Following a screening period of 2 weeks, patients with active PsA will be enrolled into a (1 : 1) 4-week randomized double-blind, placebo-controlled treatment period. After the second biopsy (at 4 weeks), all patients will receive adalimumab (Humira). Patients are allowed to use concomitant NSAIDs, corticosteroids (prednisone equivalent ≤ 10 mg/day) and methotrexate, provided the dose has been stable for at least 4 weeks prior to baseline.

Biopsies of one target skin lesion will be obtained before administration (preferable from a sun-protected area) of study drug at baseline, and after 4 weeks of treatment (a total of 4 skin biopsies). Synovial biopsies of a clinically inflamed joint (knee, wrist or ankle) will be obtained by arthroscopy before administration of study drug and after 4 weeks of treatment (a total of 2 synovial biopsies). The baseline visit and first arthroscopy *must* be within 3 days before the first administration of study medication. After 4 weeks the arthroscopy will be repeated in the same joint.

A clinical evaluation of both joint and skin symptoms will be repeated after 4 and 12 weeks of treatment. Patients will be seen for efficacy and safety assessments in accordance with standard guidelines for clinical practice during the entire study.

In total there will be 4 study visits: screening, baseline, week 4 and week 12.

There will be a ± 3-day deviation for all return visits. All visits will be fixed with reference to the baseline visit.

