### **Statistical basis for sample size**

Only limited knowledge exists on the primary variables used in this study, i.e. the immunohistochemical changes in synovial tissue and skin. Therefore, a formal estimate of the sample size is not possible. Twenty-four male and female subjects with psoriatic arthritis will be recruited to the study, based on our previous experience in comparable studies in RA [14,15] and psoriatic arthritis [10,11,17,18]. The number of subjects is based upon the desire to gain adequate information, while exposing as few subjects as possible to study procedures. Information gained from this study will be used to power future studies.

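### A normality check picks one test and an unconditional ANCOVA adds a second for every endpoint, with no statement of which result decides

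*Protocol*

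**What the plan says.** Protocol, Statistical methods, contains three statements about how the same endpoints are evaluated.

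- The opening sentence lists, among the things to be evaluated, "the changes in the synovial features and clinical parameters after treatment with adalimumab for 4 weeks". It names no comparator.
- A test is then selected by a check of the data: "The findings will be tested for normal distribution. If this requirement is not fulfilled, appropriate non-parametric methods will be used".
- A model is then added on top: "In addition, each of the end points will be statistically analyzed using an analysis of covariance (ANCOVA) model". Its terms are treatment as a fixed effect and the baseline value as covariate, and its stated purpose is the difference between treatments. It does not depend on the normality check, and no scale or transformation is given.

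One error rule covers everything: "All statistical tests will be two-tailed and performed at the 5% significance level". No sentence says which result is the conclusion for an endpoint.

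Protocol, Efficacy criteria, states the contrast of interest: "The effects of adalimumab compared to placebo on immunohistochemical indices".

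**The concern.** The text calls normality a requirement and sends endpoints that fail it to non-parametric methods. It then runs a normal-theory model on those same endpoints. An endpoint judged non-normal therefore gets both a rank test and an ANCOVA, each at 5%. An SAP that follows this wording inherits two answers per endpoint, and one that picks a single answer departs from the protocol.

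Two different things are at stake, depending on how the results are used. If the selected test is the one relied on, baseline information that ANCOVA would use may be thrown away, which a study of this size can ill afford. If whichever result is significant may be reported, the chance of a false positive exceeds the stated 5%. In both cases the check that chooses the test is made on about 12 patients per arm.

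**Working it through.** **Inputs from the documents**
- Sample size: "Twenty-four male and female subjects with psoriatic arthritis will be recruited to the study" (Statistical basis for sample size).
- Allocation: "patients with active PsA will be enrolled into a (1 : 1) 4-week randomized double-blind, placebo-controlled treatment period" (Design). So 24/2 = 12 per arm. Patients leaving before week 4 are replaced, so 12 is kept.
- Level: 5% two-sided (Statistical methods).
- There is no power figure to reproduce: "Therefore, a formal estimate of the sample size is not possible".

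**Assumed, because the documents give none**
- Baseline to week-4 correlation ρ of 0.3, 0.5 or 0.7.
- A true effect of 1 SD (0 under the null).
- Normal or log-normal markers.
- The selected test is a Shapiro-Wilk check in each arm, then a t-test or Mann-Whitney test between arms on change from baseline.

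**Step 1, analytic check (normal data, unit SD at both visits).** The variance of a change is 2(1−ρ) and the ANCOVA residual variance is 1−ρ². Their ratio is (1+ρ)/2, or 0.65, 0.75 and 0.85. Power ≈ Φ(1/(SD·√(2/12)) − 1.96), with √(2/12) = 0.408.
- ρ = 0.5, change: SD 1.000, 1/0.408 = 2.449, Φ(0.489) = 69%.
- ρ = 0.5, ANCOVA: SD 0.866, 1/(0.866 × 0.408) = 2.828, Φ(0.868) = 81%.
- ρ = 0.3: 54% against 73%. ρ = 0.7: 89% against 93%.

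**Step 2, simulation (6,000 trials per setting; Monte Carlo SE about 0.3 points near 5%).** ANCOVA is on the raw scale. The null columns have no change in either arm.

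| Data | ρ | Null: selected test | Null: ANCOVA | Null: either | Power: selected test | Power: ANCOVA |
|---|---|---|---|---|---|---|
| Normal | 0.3 | 5.0% | 5.3% | 8.0% | 51.0% | 66.4% |
| Normal | 0.5 | 4.6% | 4.4% | 6.7% | 64.4% | 75.3% |
| Normal | 0.7 | 5.0% | 5.2% | 7.0% | 85.2% | 88.4% |
| Log-normal | 0.3 | 4.7% | 3.5% | 6.8% | 28.5% | 43.9% |
| Log-normal | 0.5 | 4.7% | 4.0% | 6.8% | 36.9% | 50.3% |
| Log-normal | 0.7 | 4.6% | 3.1% | 6.0% | 50.8% | 63.1% |

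With an equal 0.5 SD shift in both arms, which is still no treatment effect, the either-result rate is 5.9–8.2%. Over all null settings the selected test alone stays at 4.3–5.5%. ANCOVA alone stays at 4.3–5.7% on normal data and 3.1–4.0% on log-normal data.

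**Step 3, behaviour of the check.** In these runs it declared truly normal changes non-normal in 9–10% of trials, as expected from two tests at 5% (1 − 0.95² = 9.75%). It passed 18–33% of log-normal data sets as normal. Which test is used therefore depends partly on chance.

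**Step 4, scale.** Take a log-normal marker with a true 60% reduction (log effect ln 0.4 = −0.916) and ρ of 0.3–0.5. In repeated runs, power at log SD 1.0 was 25–34% for the selected change test, 39–45% for raw ANCOVA and 58–69% for log ANCOVA. At log SD 0.6 it was 58–71%, 89–94% and 94–98%.

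**Step 5, the opening sentence beside Efficacy criteria.** One speaks of change after adalimumab and the other of adalimumab against placebo. Suppose both arms shift equally by 0.5 SD. A test of change within adalimumab, if someone ran one, would then be significant in 22–53% of trials with no treatment effect. That shows why such a change is not a drug effect. It does not show that the protocol orders the test.

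**The case against.** The strongest reply is that the protocol already points to the right analysis. Only the ANCOVA has a stated aim, the treatment difference, and Efficacy criteria names placebo as the comparator. Choice of test and transformation is commonly left to an SAP, and this is a 24-patient study meant to inform the sizing of later ones. It is true that the ANCOVA is the natural candidate. It is not designated, however, and the competing rule is written into the protocol rather than left open.

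Several stronger readings are tempting and should not be drawn.
- *That every endpoint gets a within-adalimumab test.* The opening sentence prescribes no test or p-value, covers synovial features and clinical parameters, and does not name skin histology.
- *That the plan both loses power and inflates error.* These belong to different uses of the results. If either result may be claimed, power is not lost.
- *That the normality check, or ANCOVA on skewed data, inflates error by itself.* The null columns show neither does.
- *That the check is shown to miss skew.* It was applied to changes, which are symmetric under the null even when the marker is skewed. Step 3 concerns non-normality only.
- *That log ANCOVA is proven superior.* Step 4 generates log-normal data, which favours it by construction. At log SD 0.6 the raw ANCOVA is already close.

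The change score, the Shapiro-Wilk test and the Mann-Whitney test are also assumptions, since the protocol names none of them.

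**Conclusion.** The point holds in a limited form. Statistical methods fixes two overlapping analyses of each endpoint at 5%, selects one by a normality check on about 12 patients per arm, runs the other even when that check fails, and lets neither decide.

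If the selected test decides and is run on changes, the loss against ANCOVA for a 1 SD effect is about 3 to 15 percentage points on normal data (88.4 − 85.2; 66.4 − 51.0) and 12 to 15 on log-normal data (63.1 − 50.8; 43.9 − 28.5). If either may be claimed, the error per endpoint is about 6–8% instead of 5%, which is modest. Both sizes rest on the assumed distribution, correlation and effect. They concern one endpoint at a time, and multiplicity across the synovial stains is a separate matter.

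A reader might infer from the opening sentence that a fall after adalimumab will count as evidence of drug effect. It should not be read that way, but the text does not prescribe such a test. This is an inexpensive improvement that should be made. It does not invalidate the design.

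**What to change.** Amend Protocol, Statistical methods, and carry the change into the SAP.

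1. State that the between-arm ANCOVA already described (treatment plus baseline) is the one deciding analysis for each endpoint, reported as a treatment difference with 95% CI.
2. Set the scale in advance by endpoint type. Use the log scale for immunohistochemical cell counts and stain scores, with a pre-set constant for zeros, reported as an adalimumab/placebo ratio. Use the original scale or a rank-based ANCOVA, chosen beforehand, for joint counts, PASI, BSA, VAS, HAQ and the 5-point global assessments, where a log ratio is unsuitable.
3. Delete the normality check as a rule for choosing the test.
4. Where the deciding ANCOVA is not itself rank-based, keep a rank-based ANCOVA as sensitivity analysis only.
5. Show within-arm changes descriptively, without p-values, and word the opening sentence so that the comparison with placebo is explicit.

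The cost is a protocol text change and the matching SAP wording, with no added patients, visits or biopsies. Tissue results will be ratios of geometric means rather than raw differences, and those with zeros will depend somewhat on the chosen constant.

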# 5. ETHICAL AND LEGAL ASPECTS

## **Good clinical practice**

The procedures set out in this study protocol are designed to ensure that the sponsor and the investigator abide by the principles of the good clinical practice guidelines of the European Community and the Declaration of Helsinki in the conduct, evaluation and documentation of this study. The study will also be carried out in keeping with local legal requirements.

## **Informed consent of patient**

Before undergoing any study procedure, the patient must have given his/her written informed consent to participate after the nature, scope and possible con­sequences of the clinical study have been explained in an understandable way. The patient will also be given an information sheet about the study and a copy of the signed informed consent form. The terms of the consent and when it was obtained must also be documented in the case record form.

## **Approval of study protocol**

Before the start of the study, the study protocol and/or other appropriate documents will be submitted to the ethics committee and/or the authori­ties, in accordance with local legal require­­ments.

## **Confidentiality**

All patient names will be kept secret. The number al­lotted to them during the study will identify patients throughout documentation and evaluation. The patients will be told that all study findings will be stored and handled in strictest confidence.

The signed informed consent forms remain with the investigator. By signing the declaration in Section 10 of this study protocol, the investi­gator agrees to obtain a correctly completed informed consent form for each patient included in the study. He/she also agrees to allow these to be inspected on request. The investiga­tor will maintain a personal list of patient numbers and patient names to enable records to be found at a later date. Both the consent forms and the personal list of patient numbers will be kept for 15 years.

## **Liability and insurance**

The civil liability of the investigator, the persons instructed by him/her and the hospital, practice or institute in which they are employed and the li­ability of AMC Medical Research B.V. (AMR) in respect of financial loss due to personal injury and other damage which may arise as a result of the carrying out of this study are governed by the applicable law.

The AMR has taken out reasonable third-party liability insurance cover. As a precautionary measure, the investigator, the persons instructed by him/her and the hospital, practice or institute are included in such cover in respect of work done by them in carrying out this trial to the extent that the claims are not covered by their own professional indemnity insur­ance.

Such insurance covers claims provided that:

- the instructions and procedures laid down in the study protocol are followed precisely and the investigator acts with the necessary care
- the patients do not undergo any other medical treatment without the previous consent of the investigator and that the investigator has in­formed patients to that effect
- the patient informs the investigator immediately of any unforeseeable adverse events
- the physical injury or other damage does not arise as a result of any gross negligence, willful act or omission

## **Use of study findings**

By signing the study protocol, the investigator agrees with the use of results of the study for the purposes of national and international registra­tion, publication and information for medical and pharmaceutical professionals. If necessary, the authorities will be notified of the investigator­'s name, address, qualifications and extent of involvement.

The findings of this study may be published in a scientific jour­nal and pre­sented at scientific meetings.

# 6. PROTOCOL AMENDMENTS

Amendments should be made only in exceptional cases once the study has star­ted. Changes must be agreed to in writing, and signed, by all parties concerned. The changes then become part of the study protocol.

The medical ethics committee must be informed of all amendments and if necessary approval must be sought for ethical aspects. Approval must also be obtained from the authorities if necessary.

**APPENDIX 1**

| **VRAGENLIJST TER BEOORDELING VAN DE GEZONDHEID (HAQ)** | | | | |  | | | | | | | |
| --- | --- | --- | --- | --- | --- | --- | --- | --- | --- | --- | --- | --- |
| **Initialen**______________________________________**Datum**_____________________________ | | | | |  | | | | | | | |
| Met deze vragen willen we te weten komen hoe uw ziekte uw dagelijks functioneren beïnvloedt. Eventuele opmerkingen kunt u aan de achterzijde van deze bladzijde opschrijven.  **Kruis a.u.b. het antwoord aan dat het beste weergeeft waartoe u IN DE AFGELOPEN WEEK doorgaans in staat bent geweest:** | | | | |  | |  | |  | |  | |
| **AANKLEDEN & PERSOONLIJKE VERZORGING**  Was u in staat om: | Zonder enige  moeite | Met  ENIGE  moeite | Met  VEEL  moeite | Niet in staat  om het  te doen |  | | | | | | | |
| - Uzelf aan te kleden, met inbegrip van schoenveters strikken en knopen dichtdoen? |  |  |  |  |  | | | | | | | |
| - Uw haar te wassen? |  |  |  |  |  | | | | | | | |
|  | | | | |  |  | |  | |  | |  |
| **OVEREIND KOMEN**  Was u in staat om: |  |  |  |  |  | | | | | | | |
| - Op te staan uit een rechte stoel zonder leuningen? |  |  |  |  |  | | | | | | | |
| - In en uit bed te komen ? |  |  |  |  |  | | | | | | | |
|  | | | | |  |  | |  | |  | |  |
| **ETEN**  Was u in staat om: |  |  |  |  |  | | | | | | | |
| - Uw vlees te snijden? |  |  |  |  |  | | | | | | | |
| - Een vol kopje of glas naar uw mond te brengen? |  |  |  |  |  | | | | | | | |
| - Een onaangebroken pak melk te openen? |  |  |  |  |  | | | | | | | |
|  | | | | |  |  | |  | |  | |  |
| **LOPEN**  Was u in staat om: |  |  |  |  |  | | | | | | | |
| - Buitenshuis op vlakke grond te lopen? |  |  |  |  |  | | | | | | | |
| - Vijf treden op te lopen? |  |  |  |  |  | | | | | | | |
|  |  |  |  |  |  | | | | | | | |
| **Kruis a.u.b. elk hulpmiddel of gebruiksvoorwerp aan dat u gewoonlijk bij bovengenoemde bezigheden gebruikt:**   Wandelstok  Hulpmiddelen bij het aankleden (haakje om knopen dicht te doen of om ritsen te sluiten, schoenlepel met verlengd handvat, etc.)   Looprek of rollator  Speciaal aangepaste gebruiksvoorwerpen   Krukken  Speciaal aangepaste stoel   Rolstoel  Anders (te weten:___________________________) | | | | |  | | | | | | | |
| **Kruis a.u.b. alle bezigheden aan waarbij u gewoonlijk hulp van iemand anders nodig heeft:**   Aankleden en persoonlijke verzorging  Eten   Overeind komen  Lopen | | | | |  | | | | | | | |

| **Kruis a.u.b. het antwoord aan dat het beste weergeeft waartoe u IN DE AFGELOPEN WEEK doorgaans in staat bent geweest:** | | | | |  |  |  |  |
| --- | --- | --- | --- | --- | --- | --- | --- | --- |
| **HYGIËNE**  Was u in staat om: | Zonder enige  moeite | Met  ENIGE  moeite | Met  VEEL  moeite | Niet in staat  om het  te doen |  | | | |
| - Uw hele lichaam te wassen en af te drogen? |  |  |  |  |  | | | |
| - Een bad te nemen? |  |  |  |  |  | | | |
| - Op het toilet te gaan zitten en er weer vanaf te komen? |  |  |  |  |  | | | |
| **BEREIK**  Was u in staat om: |  |  |  |  |  | | | |
| - Een voorwerp van ± 2 kilo (bijv. een pak waspoeder) van een plek vlak boven uw hoofd te pakken en neer te zetten? |  |  |  |  |  | | | |
| - Te bukken om kleding van de vloer op te rapen? |  |  |  |  |  | | | |
| **GRIP**  Was u in staat om: |  |  |  |  |  | | | |
| - Autodeuren te openen? |  |  |  |  |  | | | |
| - Potten te openen die al een keer open gemaakt zijn? |  |  |  |  |  | | | |
| - Kranen open en dicht te draaien? |  |  |  |  |  | | | |
| **ACTIVITEITEN**  Was u in staat om: |  |  |  |  |  | | | |
| - Boodschappen te doen en te winkelen? |  |  |  |  |  | | | |
| - In en uit een auto te stappen? |  |  |  |  |  | | | |
| - Karweitjes te doen zoals stofzuigen of tuinieren? |  |  |  |  |  | | | |
| **Kruis a.u.b. elk hulpmiddel of gebruiksvoorwerp aan dat u gewoonlijk bij bovengenoemde bezigheden gebruikt:**    Verhoogde WC-bril  Handgreep in bad   Zitje in het bad  Gebruiksvoorwerpen met een verlengd handvat om dingen te kunnen pakken    Pot-opener (voor potten die  Gebruiksvoorwerpen met een verlengd   al eens geopend zijn) handvat voor in de badkamer (bijv. een borstel).   Anders (te weten:__________________________) | | | | |  | | | |
| **Kruis a.u.b. alle bezigheden aan waarbij u gewoonlijk hulp van iemand anders nodig heeft:**   Hygiëne  Grip en het openen van dingen   Bereik  Boodschappen en huishoudelijke karweitjes | | | | |  | | | |
|  | | | | |  | | | |

**APPENDIX 2**

**VAS algehele ziekteactiviteit**

Hoe voelt u zich als u alle aspecten van de reuma (zoals ochtendstijfheid, pijn, zwelling, en beperkingen in het algemeen) laat meewegen?

*Wilt u een verticaal streepje zetten op onderstaande lijn?*

### Zeer goed _____________________________________________Zeer slecht

###

0 mm 100 mm

**VAS pijn**

Hoeveel pijn heeft u IN DE AFGELOPEN WEEK vanwege uw ziekte gehad?

*Wilt u een verticaal streepje zetten op onderstaande lijn?*

### Helemaal ___________________________________________ ___ Extreem

### geen pijn veel pijn

0 mm 100 mm

**Evaluatie algehele ziekteactiviteit (patiënt)**

Beoordeling **patiënt** van zijn/haar algehele ziekteactiviteit:

Hoe voelt u zich als u alle aspecten van de reuma (zoals ochtendstijfheid, pijn, zwelling, en beperkingen in het algemeen) laat meewegen?

1 = erg goed

2 = goed

3 = redelijk

4 = slecht

5 = erg slecht

